## Methods/design

### Study Design

This is a double-blind, placebo-controlled, randomised, multicenter clinical trial to evaluate the efficacy of probucol and cilostazol combination therapy compared with cilostazol alone in the prevention of coronary plaque progression (Figure 1). A total of 118 patients (see Sample size calculation, below) will be enrolled at five PCI centers in Korea. After enrollment and baseline investigation with IVUS and VH to establish index non-PCI target intermediate lesions and stented PCI target lesions, patients will be evaluated in clinical follow-up visits at 1, 3, 6, and 9 months. In the final 9-month follow-up examination, patients will be evaluated by IVUS and VH to assess plaque volume and plaque composition in index non-PCI target intermediate lesions, and measure neointimal hyperplasia in index stented PCI target lesions. Lipid profiles, to include total cholesterol, LDL, HDL, triglyceride, apolipoprotein A-1 and B, LDL particle size and HDL subfractions, and biomarkers associated with atherosclerosis, including high-sensitivity C-reactive protein (hsCRP), oxidized LDL, VCAM-1, von Willebrand factor (vWF) and lipoprotein (a) [Lp(a)], will be measured at enrollment, and at 1- and 9-month follow-up examinations. The trial algorithm is shown in Figure 1. This is an investigator-initiated clinical trial with grant support from Korea Otska Pharmaceutical Co. Ltd (Seoul, Korea). Other than providing financial support, the company is not involved in developing study protocols or study processes, including site selection, management, and data collection and analysis. The study is performed according to the principles of the Declaration of Helsinki and according to common guidelines for clinical trials (ICH-GCP). The authors are solely responsible for the design and editing of this paper and its final content. The trial protocol has been approved by the local institutional review boards of each patient-enrolling center, and has been registered at http://www.clinicaltrials.gov (NCT01031667). Patient information, blood samples, and IVUS, VH and coronary angiogram images will be coded with the identification number of this study; investigators are blinded to patient identifying information, which has been replaced with a coded number.

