### Study end points

The primary end point is the change in the plaque volume of index intermediate lesions between baseline and 9-month follow-up.

The secondary end points include the following:

• Plaque composition change by VH

• Clinical outcomes (death, myocardial infarction, target vessel revascularization)

• Neointimal volume obstruction at index PCI target lesions

• Blood lipid composition (total cholesterol, LDL, LDL particle size, HDL, HDL subfractions, apolipoprotein A-1 and B)

• Biomarkers (hsCRP, VCAM-1, oxidized LDL, Lp(a), vWF)

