### Statistical considerations

#### Sample size calculation

The calculation of the sample size was based on an in-equality design and a two-sample, two-sided test. Assuming a standard deviation of 8%, an α-level of 0.05 and a statistical power of 80%, 41 patients are required for each group (combination therapy, cilostazol monotherapy) to demonstrate a 5% difference in the mean plaque volume in a 10-mm segment with the greatest disease severity of the index intermediate lesion. Making allowance for a drop-out rate of 30% increases the number of patients required for each group to 59. The treatment difference and standard deviation assumptions are based on previous clinical and animal studies. Several IVUS studies have successfully demonstrated the effect of statins in reducing plaque volume. Yokoyama et al. [22] showed a 3.2% reduction in plaque volume in patients treated with atorvastatin (10 mg/day) for 6 months. The ASTEROID trial achieved about a 25% reduction in the normalized total atheroma volume using rosuvastatin (40 mg/day) for 24 months [28]. Recently, Tardif at al. [29] reported that a 12-month therapy with succinobucol, an analog of probucol, reduced the plaque volume of index lesions by 1.5%, whereas the control group showed no significant change in plaque volume. Notably, the results of an animal study evaluating the antiatherogenic effects of cilostazol and probucol showed that combination therapy was more effective in reducing the size of atherosclerotic lesions than was administration of either drug alone [18]. For this reason, we expect that cilostazol and probucol combination therapy will be more potent in reducing plaque volume than succinobucol, and hypothesize that the combination therapy could achieve a reduction in plaque volume 5% greater than that achieved by cilostazol monotherapy.

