### Statistical analysis

All statistical analyses will be carried out by an independent organization, ADM Korea Inc. All primary and secondary end points will be analyzed on a modified intention-to-treat basis (all randomized subjects who receive at least one dose of study drug and have IVUS and VH measurements at baseline and at the study end point). The primary efficacy analysis will be performed using an analysis of covariance model, adjusting for baseline values. If the data are not distributed normally, a nonparametric analysis of covariance analysis will be used. All continuous secondary efficacy variables will be analyzed using similar methods. The composite end point of cardiovascular events will be analyzed by comparing Kaplan-Meier event rates using a log-rank test. Independent predictors of major adverse cardiac events (MACE) were determined using a multiple logistic regression analysis.

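### The planned multiple logistic regression for predictors of MACE has no event count behind it, and at assumed event rates up to 20% the trial cannot support even three predictors

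*Protocol article*

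**What the plan says.** All statements are in the protocol article.

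- Statistical analysis, last sentence: "Independent predictors of major adverse cardiac events (MACE) were determined using a multiple logistic regression analysis". It is in the past tense, unlike the rest of the section. It names no predictors and does not call the analysis exploratory.
- Statistical analysis, the sentence before: "The composite end point of cardiovascular events will be analyzed by comparing Kaplan-Meier event rates using a log-rank test".
- Statistical analysis, analysis set: every primary and secondary end point is analysed in randomised patients who took at least one dose and have both IVUS and VH at baseline and at the end of the study.
- Sample size calculation: this is a two-sided comparison of two groups, and its target is a 5% difference between them in plaque volume. The article puts it thus: "Assuming a standard deviation of 8%, an α-level of 0.05 and a statistical power of 80%, 41 patients are required for each group". Inflation for 30% drop-out then gives 59 per group.
- Study end points, one secondary item: "Clinical outcomes (death, myocardial infarction, target vessel revascularization".
- Study Design: "A total of 118 patients (see Sample size calculation, below) will be enrolled at five PCI centers in Korea". Clinical visits run to 9 months.

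The article gives no expected MACE rate and no expected number of events. None of its stated aims or end points asks which patient factors predict MACE.

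**The concern.** The information in a logistic model comes mainly from the number of events, not the number of patients. This trial was sized for a continuous imaging measure, and its small size follows from that. The article nevertheless commits to a multivariable model of a clinical event that may be uncommon over nine months, in a population that excludes acute infarction treated by primary or rescue PCI. With few events per coefficient, odds ratios are imprecise and tend to be exaggerated. A result labelled an independent predictor, coming from a randomised trial, is likely to be read as a finding.

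The analysis set aggravates this. A patient who dies before the 9-month imaging cannot have end-of-study IVUS and VH. Taken literally, the set removes early deaths from an outcome that has death as its first component, and it reduces the number of patients available for the model.

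**Working it through.** **1. The plan's own sample size.** With SD 8, difference 5, two-sided α 0.05 and power 80%:

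n per group = 2 × (1.960 + 0.842)² × 8² / 5² = 2 × 7.85 × 2.56 = 40.2, rounded up to 41.

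Drop-out: 41 / (1 − 0.30) = 58.6, rounded up to 59. Total: 2 × 59 = 118. Evaluable: 2 × 41 = 82. The stated figures reproduce, and none of them involves an event rate.

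**2. Assumptions needed.** MACE is taken to be the composite of the three clinical outcomes listed under Study end points. The documents give no rate, so 3% to 20% over 9 months is assumed. The same range is applied to both sets. Excluding deaths would change the rate among the 82 by an amount that the documents do not allow me to estimate.

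**3. Expected events and events per predictor.** Events = N × rate; events per predictor = events / number of predictors.

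- N = 118: 118 × 0.03 = 3.5, up to 118 × 0.20 = 23.6. With three predictors: 1.2 to 7.9 each. With five: 0.7 to 4.7.
- N = 82: 82 × 0.03 = 2.5, up to 82 × 0.20 = 16.4. With three predictors: 0.8 to 5.5 each. With five: 0.5 to 3.3.

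Taking ten events per predictor as a rough guide, the MACE rate required is 10k / N for k predictors:

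| Predictors | N = 118 | N = 82 |
|---|---|---|
| 1 | 8.5% | 12.2% |
| 2 | 16.9% | 24.4% |
| 3 | 25.4% | 36.6% |
| 5 | 42.4% | 61.0% |

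**4. How a fitted model would behave.** Null simulation, 600 data sets per row, with five assumed predictors that have no true effect: treatment, two binary factors at 30% prevalence, and two continuous factors. Separation was checked by linear programming. The last two columns refer to runs in which the model could be fitted.

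| N | MACE rate | Separation | Any predictor p < 0.05 | Any binary odds ratio > 3 or < 1/3 |
|---|---|---|---|---|
| 118 | 3% | 55% | 10% | 56% |
| 118 | 5% | 33% | 14% | 49% |
| 118 | 10% | 5% | 19% | 38% |
| 118 | 15% | 1.5% | 22% | 24% |
| 118 | 20% | 0.2% | 20% | 14% |
| 82 | 3% | 69% | 5% | 55% |
| 82 | 5% | 53% | 7% | 56% |
| 82 | 10% | 15% | 16% | 48% |
| 82 | 15% | 4% | 16% | 37% |
| 82 | 20% | 1% | 20% | 32% |

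For comparison, five independent tests at 0.05 give at least one false positive with probability 1 − 0.95⁵ = 23% at any sample size.

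**5. Analysis set.** Clinical outcomes are a secondary end point, and the analysis set is stated to apply to all secondary end points. That set requires end-of-study imaging. Together these rules exclude every death before nine months, both from the logistic model and, on the same wording, from the log-rank comparison.

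**The case against.** The strongest case on the other side has five parts.

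- **The rate is assumed.** A reader might infer that the trial is expected to yield only a handful of events. The document does not say so. At 15% to 20% there would be 12 to 24 events across the two sets. This stands, and the conclusion is therefore given as a range.
- **Separation is not inevitable.** A reader might infer that the model will fail to fit. In the simulation separation is common only at about 5% or below, and affects 4% of runs or fewer at 15% and above. This stands.
- **Spurious significance is not shown to be excessive.** A reader might conclude that any reported predictor will be noise. The simulated 5% to 22% does not exceed the 23% expected from testing five null factors at any sample size, and the absence of true effects was a simulation setting, not a property of the trial. This stands. What few events do produce is unstable, extreme odds ratios.
- **Logistic regression is not in conflict with the log-rank test.** One explores predictors and the other compares arms. Within patients who have 9-month imaging there is little censoring, so a binary outcome is defensible there. This stands for the set as written. It weakens once all randomised patients are analysed, because some may have incomplete follow-up.
- **The predictor list and model-size limit may be in an unseen SAP.** This is fair, and their absence is not counted as a fault. But a SAP cannot supply events, and the shortfall already appears at three predictors.

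The Discussion also names the small study population as a limitation, though without linking it to this model.

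**Conclusion.** The concern holds in limited form. The article commits to a multivariable model of MACE that no stated event count supports. For any assumed 9-month rate from 3% to 20%, three predictors have at most 7.9 events each in 118 patients or 5.5 in 82, so the odds ratios would be unstable and often exaggerated. This rests on the assumed rate range, on MACE being the listed composite, and on ten events per predictor as a rough guide. The simulated percentages also depend on the five predictors chosen.

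The exclusion of early deaths follows from the article's wording and needs no assumed rate.

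The weight is moderate. The primary analysis of plaque volume and the sample size are not touched. What is at risk is the credibility of a secondary report on clinical events.

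**What to change.** 1. Delete the logistic-regression sentence. Alternatively, keep it as an explicitly exploratory analysis with a penalised fit (for example Firth) and a limit on predictors set in advance as a function of the observed event count. At one predictor per ten events, the assumed range allows none to two in 118 patients and none to one in 82. Penalisation reduces bias but adds no information, so it does not replace the limit.
2. State that clinical events are analysed in all randomised patients, whether or not 9-month IVUS and VH were obtained.
3. Report counts per arm and per component with exact 95% confidence intervals, together with the planned Kaplan-Meier and log-rank comparison, and label these results descriptive.

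Cost: a few sentences of text. Full deletion loses an exploratory predictor analysis that serves no stated objective. Analysing all randomised patients requires clinical follow-up of those who miss the final imaging. The primary analysis does not change.

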## Discussion

SECURE has been designed to test the hypothesis that combination therapy with cilostazol and probucol is more effective in reducing plaque volume than cilostazol monotherapy. The effectiveness of probucol against atherosclerosis has been demonstrated in previous clinical trials. In the Fukuoka Atherosclerosis Trial (FAST), the patient group treated with probucol (500 mg/day) showed significantly reduced intima media thickness in the common carotid artery compared to the control group [30]. In an IVUS substudy of the Canadian Antioxidant Restenosis Trial (CART-2), significant atherosclerosis regression was observed in patients treated with the probucol analog succinobucol, whereas no significant change in plaque volume occurred in the placebo group [29]. In the Probucol Observational Study Illuminating Therapeutic Impact on Vascular Events (POSITIVE), long-term probucol treatment effectively prevented secondary cardiovascular events in a higher-cardiovascular-risk heterozygous familial hypercholesterolemia population without causing severe adverse effects [31]. Cilostazol has also demonstrated diverse antiatherogenic properties in previous studies [11-14]. Recent animal studies have suggested that probucol and cilostazol may synergize in the prevention of atherosclerosis by suppressing inflammatory reaction and promoting cholesterol efflux [18,19].

In the SECURE study, in addition to changes in plaque volume, we will also evaluate the potential of combination therapy to stabilize coronary plaques by altering their composition. Virtual Histology, a software system that enables a spectral analysis of radiofrequency backscatter IVUS, was recently developed to analyze plaque composition, providing information on fibrous, fibrofatty, dense calcium, and necrotic core components [20]. VH findings have been validated using various human atherosclerotic plaque tissues [21]. Different statins and darapladip, a direct lipoprotein-associated phospholipase A(2) inhibitor, have shown coronary plaque-stabilizing effects by reducing the necrotic core [22-25]. The SECURE study will also confirm whether the combination therapy is superior to cilostazol alone in decreasing neointimal hyperplasia after implantation of a drug-eluting stent. Previous studies have shown that both probucol and cilostazol are effective in preventing restenosis after PCI with or without stent implantation [2,10,32]. In addition, Sekiya et al. [17] demonstrated that cilostazol and probucol combination therapy reduced restenosis after stent implantation more effectively than either cilostazol or probucol alone.

Another focus of the SECURE study is on changes in lipid composition associated with probucol and cilostazol combination therapy. Generally, high LDL and low HDL cholesterol levels are regarded as major risk factors for coronary artery disease. However, within LDL and HDL cholesterols are subfractions with different particle sizes and different roles in the metabolism of lipids [33,34]. Although still controversial, small, dense LDL is thought to be more atherogenic in conjunction with other features of metabolic syndrome, such low HDL and high triglyceride levels [33]. Generally, the larger triglyceride-rich HDL2 subfraction is thought to confer better protection against coronary artery disease than the small HDL3 fraction [34]. In a recent trial, the CETP inhibitor torcetrapib, which raised HDL-C levels by approximately 70%, showed a paradoxical increase in cardiovascular disease outcomes [35]. Thus, a simple elevation of HDL cholesterol levels does not necessarily translated into protection from atherosclerosis. Probucol is thought to reduce HDL cholesterol by enhancing reverse cholesterol transport through increased expression of the hepatic HDL-receptor SR-B1 and activation of CETP [4-6]. Hepatic over-expression of SR-B1 increases hepatic uptake of HDL cholesterol resulting in increased biliary excretion of cholesterol. Probucol is known to increase the levels and activity of CETP [4,5]. Activation of CETP increases transfer of cholesterol esters from HDL to triglyceride-rich lipoprotein particles in exchange for triglyceride, thereby reducing the circulating HDL cholesterol concentration. Whether CETP is anti- or proatherogenic is currently not fully understood. Potential antiatherogenic roles of CETP include HDL remodeling, with increased efflux of lipid-poor apolipoprotein A-I in exchange for cholesterol; and shuttling of cholesteryl esters to apolipoprotein B-containing lipoproteins, namely LDL, intermediate density lipoprotein (IDL), and very low density lipoprotein (VLDL), for excretion by the liver. In the SECURE study, we will investigate lipid parameters, such as LDL and HDL subfractions, and apolipoprotein A1 and B, as well as total cholesterol, triglyceride, HDL, and LDL. In addition, we will evaluate the effects of probucol and cilostazol combination therapy on the atherosclerosis biomarkers, oxidized LDL, VCAM-1, and vWF.

Possible major limitations of the SECURE study will be the relatively small number of study population and the short interval duration for follow-up IVUS study. However, several small clinical studies have shown significant plaque reduction with change of plaque composition despite relatively short period (6 or 12 months) of follow-up [22,23,25]. Thus, if probucol combined with cilostazol has strong antiatherosclerotic effects as shown in previous clinical and experimental studies, we think the SECURE study will be able to demonstrate them in terms of the primary or secondary endpoints.

In conclusion, the SECURE study will be the first double-blind, randomized, controlled multicenter clinical trial using VH-IVUS to investigate the effects of probucol and cilostazol combination therapy on the progression and composition of coronary artery plaques. Furthermore, the SECURE study will deliver important information on the effects of combination therapy on lipid composition and biomarkers related to atherosclerosis, thereby providing insight into the mechanisms underlying the prevention of atherosclerosis progression by cilostazol and probucol.

## Trial registration number

National Institutes of Health Clinical Trials Registry (ClinicalTrials.gov identifier #NCT01031667).

## Abbreviations

LDL: low-density lipoprotein; CAD: coronary artery disease; PCI: percutaneous coronary intervention; HDL: high density lipoprotein; CETP: cholesteryl ester transfer protein; SR-B1: scavenger reverse cholesterol class B type 1; VCAM: vascular cell adhesion molecule; MCP: monocyte chemoattractant protein; IVUS: intravascular ultrasound; VH: Virtual Histology; hsCRP: high-sensitivity C-reactive protein; vWF: von Willebrand factor; Lp(a): lipoprotein (a); Lp-PLA2: lipoprotein-associated phospholipase A2; MACE: major adverse cardiac events
